## Abstract

**Background:**

Despite the benefits of breastfeeding, early weaning is a reality, so less than 50% of children worldwide and in Brazil are on exclusive breastfeeding in the sixth month of life. A strategy to counteract this scenario is breastfeeding counseling. This study aims to verify the effectiveness of individualized counseling by nurses trained in breastfeeding counseling, on the duration of exclusive breastfeeding, compared to standard care.

**Methods:**

Multicenter, randomized, parallel, and open clinical trial, with primiparous women aged over 18 years, hospitalized in rooming-in wards at participating centers and hemodynamically stable, aware, and oriented, who had a single-fetus pregnancy and gave birth, regardless of the type of delivery, with live child, gestational age of 37 to 42 weeks and birth weight greater than 2500 g. The women will be initially approached in rooming-in wards and, upon consent to participate in the study, will be allocated through randomization by blocks composed of eight participants in two groups: intervention and control. The randomization lists will be organized by a central without involvement with the study, which will manage the allocation groups and be prepared in the Randon® program. Women allocated to the intervention group will receive breastfeeding counseling by trained nurses, and those in the control group will receive standard care at the center participating in the study.

**Discussion:**

The results can contribute to breastfeeding by evidencing possible exclusivity and duration of the counseling trained nurses provide.

**Trial registration:**

REBEC RBR-4w9v5rq (UTN: U1111-1284–3559) (https://ensaiosclinicos.gov.br/rg/RBR-4w9v5rq). Posted on March 20, 2023.

**Supplementary Information:**

The online version contains supplementary material available at 10.1186/s13063-023-07490-y.

## Introduction

The World Health Organization defines breastfeeding counseling as support for mothers and newborns (NB) provided by health professionals, helping the woman and her family in decision-making and overcoming possible difficulties [1, 2]. It had its first description in 1993. It is based on dialogic interaction between counselors and women who breastfeed or intend to breastfeed. Thus, they aim to empower and support women in breastfeeding, respecting their reality and personal desires [1–3]. It is a horizontal, person-centered approach that goes beyond clinical management and guidelines for successful breastfeeding, meeting the principles of authenticity, positive feelings, and empathy, based on therapy centered on the needs of the client (counseling) by Carl Rogers and listening without judgment [1, 2].

To implement counseling, professionals need specific training, with a theoretical and practical workload ranging from 20 to 40 h, where listening and learning skills are worked on, in addition to increasing confidence and providing support to women who breastfeed or want to breastfeed. Although counseling is considered a light technology to support breastfeeding, not all breastfeeding support is provided through this approach [3].

Thus, despite the description of positive results with the implementation and strategy dating from the 1990s, it is observed that there still needs to be a description of protocols for this intervention, especially concerning its application during the hospitalization of the dyad in rooming-in wards. It is important to emphasize that it differs from the process of health education and clinical management focused on breastfeeding, justifying the originality and the need to carry out this study.

The need to test interventions to promote breastfeeding is reinforced since the perception of support from mothers during hospitalization significantly predicts exclusive breastfeeding [4]. Thus, providing an evidence-based intervention to support hospitalized mothers is critical [4].

A systematic review study with meta-analysis pointed out the positive effect of the intervention in reducing weaning before the sixth month (RR = 0.91) and before 6 weeks (RR = 0.87). However, it is considered moderate-quality evidence due to the significant heterogeneity of the analyzed studies [3].

The literature points out as results of counseling: increased rates of exclusive breastfeeding [5–8]; and an increase in the duration of breastfeeding, including mixed breastfeeding [9, 10] and in the exclusive and mixed forms [11]. Some studies, however, did not identify differences with its implementation [12, 13], but the great sample heterogeneity is highlighted, related to the number of maternal pregnancies; gestational age; birth weight, and, as pointed out, the absence of specific protocols for its performance.

In addition, no clinical, randomized, multicenter Brazilian trial has been identified that studied the effectiveness of individualized counseling carried out by nurses trained in counseling during the duration of exclusive breastfeeding. Therefore, this research project will test the following alternative hypothesis: individualized counseling provided by trained nurses is effective in the duration of exclusive breastfeeding compared to standard care. As a null hypothesis: individualized counseling performed by trained nurses is ineffective in the duration of exclusive breastfeeding, compared to standard care.

Therefore, this study aims to verify the effectiveness of individualized counseling performed by trained nurses on the duration of exclusive breastfeeding and on occurrence of breast complications compared to standard care.

## Methods

This clinical trial has the following specific objectives:Compare the percentage of occurrence of nipple-areolar lesions in the first and second weeks of life for the intervention and control groups;Compare breast complications in the first 2 weeks based on mother reports and compare results between groups;Compare the percentage of exclusive breastfeeding in the first, fourth, and sixth month in both groups;Evaluate postpartum depression scores at different times (1, 4, and 6 months) and compare the occurrence between the two groups;Compare the rate of hospitalizations and occurrence of childhood illnesses at 2, 4, and 6 months of life, according to the type of breastfeeding and between groups;Compare the percentage of weaning between groups;Evaluate the care complexity of the dyads (minimal, intermediate, semi-intensive, and intensive care) participating in the study, based on a validated scale, andPresent the performance scores of the nursing mother and the baby during breastfeeding during hospitalization in the rooming-in wards, in the two study groups, based on a validated scale (LACTH).

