### Inclusion and exclusion criteria for participants

Will be included in the study, primiparous, aged over 18 years; who were pregnant with a single fetus, with live birth, gestational age of 37 to 42 weeks, birth weight greater than 2500 g, regardless of the type of delivery; who are hemodynamically stable, conscious, and oriented and admitted to the rooming-in wards, of the participating centers, at the time of allocation for the study.

Postpartum women and newborns with contraindications for breastfeeding (HIV positive; HTLV 1 and 2 positive or neoplastic treatment with chemotherapy) will not be included; infants with malformations that prevent or make breastfeeding difficult or with changes in breastfeeding mechanics (lingual frenulum); puerperal women whose infants were immediately separated after clamping the umbilical cord at birth due to maternal-neonatal complications, in which one or both were hospitalized in critical units; postpartum women transferred from other institutions or who have already been discharged (rehospitalization), postpartum women using illicit drugs, postpartum women with intellectual or sensory disabilities with a medical diagnosis. These criteria contemplate the feasibility of the intervention and the necessary follow-up to the clinical trial.

Women who are not followed up in the first month, after three unsuccessful attempts at contact and at least one contact with a family member at different times, will also be excluded if malformations or abnormalities in the mechanics of breastfeeding or changes in the mother–child bond are detected at the time of allocation.

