### Data collection instruments

The data collection instrument developed specifically for this study was submitted to content validation by eight experts with a doctorate and relevant experience in Breastfeeding Counseling, teaching, and evidence-based research.

The baseline instrument contains three parts, namely: Part I—sociodemographic variables: age; self-declared race marital status, and, if living with a partner, age, and level of education; schooling, family income, occupation, maternity leave, paternity leave, origin and presence of a companion at the time of the interview; Part II—clinical variables: smoking, coffee drinking, health problems, and medication use; Part III—obstetric variables: prenatal care and the number of consultations; guidance on breastfeeding during prenatal care and sources, including specification in case of professional guidance. Information about the delivery/birth will be collected, such as date of delivery, type of delivery, if the puerperal woman had a companion during labor and delivery; if there was early contact with the newborn, and if the mother started breastfeeding in the first hour of life. About the NB, weight, height, gestational age, and type of breastfeeding data will be collected at the time of hospital discharge.

The information will be collected through interviews and medical records.

Women allocated to the intervention group will be encouraged to answer the following open questions: How are you breastfeeding? Moreover, if she has doubts or concerns, they will be explored with: Tell me about it… Next, the following guiding question will be used: How are you feeling breastfeeding? Furthermore, in the end, you will be asked: What led you to breastfeed? The validated protocol for counseling on breastfeeding during hospitalization in rooming-in wards will be used for all responses.

For evaluation based on observation of breastfeeding, the LACTH [24] scale will be used—attachment, swallowing, type of nipple, comfort, and positioning, applied to both groups, based on observation of at least one breastfeeding.

A nipple-areolar evaluation will be performed, regarding skin color and type of nipple [27]. In case of nipple-areolar lesions detected by visual inspection, the Nipple-Areolar Lesions Classification Instrument [28] and the Nipple Trauma Score [29] will be applied.

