In the intervention group, the postpartum woman will be approached with the strategy of counseling, breast evaluation, and at least one breastfeeding and interview according to a validated protocol. Ultimately, the researcher will reinforce the subsequent contacts, which will succeed in the allocation, interspersed in the morning and afternoon, depending on time zero, until hospital discharge. In the follow-up at the hospital, an approach with a counseling strategy will be carried out, identifying doubts and potential needs. In the end, the videoscribe will be offered and reinforced about subsequent telephone contacts for follow-up and their importance.

To characterize the sampling, the researcher will complete a daily list of eligible postpartum women, included or not included, and reasons for non-inclusion.

If the researcher detects abnormalities in the mechanics of breastfeeding or changes in the mother–child bond, the care team members will be notified, and the participant must be excluded.

Follow-up interviews will be done through phone calls. The researcher will make three telephone contact attempts at different times of the day: between 12:30 pm and 1:30 pm, from 4:00 pm to 5:00 pm, or at another preferred time indicated by the participant. If the attempt is unsuccessful, the researcher will try to contact the number provided by the family member. If accepted, the researcher will apply the questionnaire, thank them, and inform a new contact within a week. Contact will be made by the researcher who collected the data with the postpartum women included to maintain the link with the postpartum women and reduce sample losses.

In the second week, the same procedures will be carried out, but at the end, the researcher will signal a new contact in 2 weeks; in the first month, he will inform that he will return in 3 months, and on the fourth month, he will inform that the next call will be in 2 months. At the end of the protocol, the researcher will close the research and thank the participant.

Postpartum women who are not followed up in the first 15 days, after three unsuccessful contact attempts and at least one contact with a family member at different times, will be excluded.

All data will be completed in Google Forms® electronic forms on tablets purchased for this purpose. Only researchers will have access to the electronic database, collection instruments, and consent forms.

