### Secondary outcomes

Nipple-areolar lesions: lesion(s) in the nipple-areolar region(s) with or without disruption of the skin barrier.Nipple or breast pain: verbal report of pain, describing its characteristics, associated with breastfeeding.Breast complications: occurrence of engorgement or mastitis.Exclusive breastfeeding in the first, fourth, and sixth months of life: exclusive breastfeeding in this period.Postpartum depression scores: measured by the Edinburgh Scale, indicated for tracking signs indicative of puerperal depression, which should be applied after the persistence of symptoms of puerperal blues, that is, with continuity of symptoms after 1 month and consistent with the birth.Hospitalizations and occurrence of illnesses in childhood: based on the mothers’ report to the telephone contact.Weaning: interruption of breastfeeding, considered early, when it occurs before 4 months of the child’s life.Care complexity of the dyads: classification into minimal, intermediate, semi-intensive, and intensive care, based on the care required by postpartum woman and newborn.Performance of the postpartum women and newborn during breastfeeding: based on the validated scale (LACTH) application.

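### Week-1 and week-2 nipple lesions and pain include those present before allocation, and the hospital examination that could separate them is not a pre-randomisation baseline

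*Protocol article*

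**What the plan says.** All places are in the protocol article.

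- **Objective (Methods, specific objectives).** The trial will "Compare the percentage of occurrence of nipple-areolar lesions in the first and second weeks of life for the intervention and control groups".
- **Definitions (Secondary outcomes).** A lesion is any "lesion(s) in the nipple-areolar region(s) with or without disruption of the skin barrier". Pain is a "verbal report of pain, describing its characteristics, associated with breastfeeding". Neither definition asks when the problem began.
- **Entry (Inclusion and exclusion criteria for participants).** Women must be "admitted to the rooming-in wards, of the participating centers, at the time of allocation for the study". No limit is set on time since delivery or first feed, and a lesion or pain at entry is not an exclusion.
- **Feeding before entry (Data collection instruments).** The baseline form asks "if the mother started breastfeeding in the first hour of life", so feeding can precede allocation.
- **Follow-up (Data collection instruments).** The week-1 and week-2 telephone calls ask about lesions or pain. No item is described that separates new problems from those already present in hospital.
- **Hospital examination (Data collection instruments).** "A nipple-areolar evaluation will be performed, regarding skin color and type of nipple". A visible lesion is then graded with a classification instrument and a trauma score, and pain is rated on a visual analogue scale.
- **Sequence (Recruitment and data collection procedures).** Consent comes first, then the call to the randomisation centre, then the breast evaluation. In the intervention arm, "the postpartum woman will be approached with the strategy of counseling, breast evaluation, and at least one breastfeeding and interview".
- **Masking (Study design; Randomization, concealment of allocation, and masking).** The trial is open, and the researchers collecting data know the allocation.

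**The concern.** A woman may already have a damaged or painful nipple when she is allocated. If the problem is still there at the week-1 call, the definitions count it, although counselling that had not yet started could not have prevented it. The reported percentage then combines two things: new problems among women who were free of them, and persistence among women who were not. A reader of the results would naturally take a statement about occurrence to concern prevention.

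The obvious remedy is to split women by their status at the hospital examination. As sequenced, that split would rest on a finding made after randomisation by someone who knows the arm and, for counselled women, during the counselling contact itself. A later analysis plan can change the outcome definition, but it cannot move the examination ahead of allocation.

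**Working it through.** **No figure to reproduce.** The article gives no lesion or pain rate, no effect size for these outcomes and no main-trial sample size, which is to follow the pilot. Every rate below is an assumption chosen for illustration.

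**Model.** Let b be the share of women with a lesion at allocation (equal between arms in expectation), s the share of those still reporting one at week 1, and p the risk of a new lesion in women free of one at allocation.

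- Observed risk in an arm = b·s + (1 − b)·p
- Observed risk difference, control minus counselling = b·(s_C − s_T) + (1 − b)·(p_C − p_T)

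If persistence is equal in the two arms, the first term vanishes and the difference is (1 − b)·(p_C − p_T), whatever the value of s. If counselling affects neither new lesions nor persistence, both terms are zero, so the definition does not create a false difference.

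**Dilution, with p_C = 30%, p_T = 20%, s = 100% in both arms:**

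| b | Control | Counselling | Difference | RR |
|---|---|---|---|---|
| 0% | 30% | 20% | 10 points | 0.67 |
| 10% | 0.10 + 0.90 × 0.30 = 37% | 0.10 + 0.90 × 0.20 = 28% | 9 points | 0.76 |
| 20% | 0.20 + 0.80 × 0.30 = 44% | 0.20 + 0.80 × 0.20 = 36% | 8 points | 0.82 |
| 30% | 0.30 + 0.70 × 0.30 = 51% | 0.30 + 0.70 × 0.20 = 44% | 7 points | 0.86 |

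**Dependence on healing, with p_C = 30%, p_T = 21% (RR 0.70, difference 9.0 points among lesion-free women) and b = 20%:**

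| Persistence, control / counselling | Control | Counselling | Difference | RR |
|---|---|---|---|---|
| 100% / 100% | 44.0% | 36.8% | 7.2 points | 0.84 |
| 50% / 50% | 34.0% | 26.8% | 7.2 points | 0.79 |
| 80% / 56% | 40.0% | 28.0% | 12.0 points | 0.70 |
| 80% / 40% | 40.0% | 24.8% | 15.2 points | 0.62 |

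The first two rows shrink the contrast. In the third, counselling reduces persistence by the same relative amount as new lesions: the RR is unchanged and the difference grows. In the fourth, the contrast exceeds the effect on new lesions on both scales.

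**Precision, for the equal-persistence case only.** I use two-sided 5% (the article does not state sidedness), the stated 95% power, and 1:1 allocation, inferred from the pilot's 10 + 10 per centre. Detecting 30% v 21% needs 607 evaluable women per arm. With 607 enrolled per arm and s = 100%:

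- b = 20%: power is 0.73 counting all lesions, and 0.90 counting new lesions among the roughly 486 lesion-free women per arm (0.80 × 607). Reaching 95% power with all lesions counted would take 1205 per arm.
- b = 40%: power is 0.47 and 0.80 respectively.

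In these cases the restricted analysis has more power despite its smaller denominator. The article does not size the trial on this outcome, so these figures show only the relative cost.

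**The case against.** A reader might infer that the trial cannot tell whether counselling prevents lesions, that the objective cannot be answered, or that the result must be pulled towards no difference. The documents do not support any of these.

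- Lesion and pain status is recorded in hospital in both arms, so new onset could be derived. For visible lesions, an inspection within a contact of about 30 minutes (Discussion) will mostly reflect the state before counselling. The timing matters more for pain ratings and for the assessor's knowledge of allocation. The sentence describing the intervention contact is also a list rather than an explicit order, and the flowcharts are not shown.
- The objective compares percentages between groups and does not claim to isolate prevention. Randomisation balances existing lesions in expectation, so the all-women contrast is a valid estimate of overall burden. The Introduction presents counselling as help with difficulties, so resolution may be part of its intended effect.
- The direction depends on what counselling does to existing lesions. Nor do existing lesions simply add one constant to both arms: a constant would leave the risk difference unchanged, whereas it shrinks by 1 − b under equal persistence.
- No sentence says outright that existing lesions count. That follows from the unrestricted definitions, and an analysis plan that is not shown may refine them. The general reference to subgroup and adjusted analyses leaves room for this.

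These points limit the concern without removing it. The text does not link the hospital examination to the week-1 and week-2 outcome, and the stated sequence puts it after allocation in both arms.

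**Conclusion.** The point holds in a limited form. As defined, the week-1 and week-2 lesion and pain comparisons measure prevalence after allocation, which combines prevention with resolution. Dilution by 1 − b rests on two assumptions: a baseline prevalence b, which the article does not give, and persistence unaffected by counselling. If counselling speeds healing, the contrast may be as large as the effect on new lesions or larger.

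The part that needs a protocol change is the timing. A baseline taken by unblinded staff after randomisation, and during the intervention in one arm, is a weak basis for separating new problems from old. The quoted objective covers lesions only; pain enters through its own secondary definition and the telephone calls. These are secondary outcomes and the duration of exclusive breastfeeding is untouched, so this is a minor but inexpensive improvement.

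**What to change.** 1. Carry out the nipple inspection and pain rating already planned for every woman after consent and before the call to the randomisation centre.
2. Keep the comparison of all women at weeks 1 and 2, adjusted for or stratified by that baseline status.
3. Report new lesions, and separately new pain, among women free of them at baseline. Show persistence among the others separately.

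The cost is a few minutes before allocation and a smaller denominator for the new-onset analysis. No new instrument is needed, and consent already precedes randomisation. Under Clinical trial status, the main trial is due to start collection after the pilot, so the change could be made by amendment before main recruitment.

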### Study design

This is a multicenter, randomized, superiority, parallel, and open clinical trial guided by the international recommendations of the Consolidated Standards of Reporting Trials [14].

The randomized clinical trial is considered the gold standard for evaluating health interventions, establishing a causal relationship, and evaluating the effectiveness of the intervention [15].

This is a superiority study, because it will determine whether the investigational intervention is superior to the comparator; parallel study, as each group of participants will be exposed to only one intervention studied (intervention or control); random, as participants will be allocated between groups, and each individual has the same probability of being selected for one group or another [16, 17]; and open, as there will be no masking of the intervention (participants and researchers) [18–21], because it would be impossible to blind this intervention for women and nurses. However, data analysis will be carried out by researchers not directly involved in data collection.

This clinical trial protocol was designed following the Standard Protocol Items: Recommendations for Interventional Trials (SPIRIT) [22] as evidenced in the checklist (see Additional File 1).

